#### Survival Outcomes

One-year OS and PFS will be analyzed using the Kaplan-Meier method with log-rank tests. A Cox proportional hazards model will be used to estimate hazard ratios.

A one-sided *P* value of <.03 will be considered statistically significant.

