**Conclusions:**

This study will evaluate the efficacy of the TSZA regimen in managing PNSCs in patients with ovarian cancer and generate clinical evidence for a new therapeutic option that improves quality of life and alleviates the symptom burden.

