### Objectives

The primary objective of this study is to evaluate the efficacy and safety of the TSZA regimen in alleviating PNSCs among patients with ovarian cancer. The secondary objectives include assessing its impact on patients’ quality of life and survival outcomes. Furthermore, the study aims to explore the characteristics of the patient population that derives benefit from the TSZA regimen for these symptoms.

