### Sample Size

A superiority design is used for this study. Given the lack of a universally established remission standard for the PNSCs derived from the MDASI-OC scale, parameters are determined based on internal pilot data and expert consensus. The remission rate for the control group at 3 months is estimated at 10%. We posited an absolute increase of 30% in the intervention group, corresponding to an expected remission rate of 40%. To ensure clinical significance, a superiority margin (*M*) of 15% is prespecified and incorporated into the sample size formula. Assuming a one-sided significance level (α) of .025 and a statistical power (1-β) of .80, calculations performed via PASS software (version 15.0; Superiority by a Margin Tests for the Difference Between Two Proportions) yielded a required sample size of 116 participants per group. Accounting for an anticipated 20% dropout rate, a minimum of 145 participants per group is required. To further enhance the robustness of the findings and to accommodate potential variability in dropout rates or covariate adjustments, the final total sample size is determined to be 316 participants (158 per group). This ensures that the actual statistical power of the final analysis set remains consistently above 80%.

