##### The European Organisation for Research and Treatment of Cancer Quality of Life Questionnaire - Core Scale

This core instrument for patients with cancer comprises 30 items. Most items are scored on a 4-point scale (1=not at all to 4=very much). Items 29 and 30, which assess overall health and quality of life, use a 7-point scale (1 to 7). The items form 15 scales: 5 functional scales (physical, role, cognitive, emotional, and social), 3 symptom scales (fatigue, pain, and nausea or vomiting), a global health status or quality of life scale, and 6 single items. All scale scores will be linearly transformed to a 0- to 100-point scale. For the functional and global health status scales, a higher score represents a better level of functioning or quality of life. For the symptom scales and single items, a higher score indicates a greater severity of symptoms or problems [29]. Assessments will be conducted at baseline and at 1, 2, 3, 6, 9, and 12 months after enrollment.

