#### Secondary Outcome Analysis

Linear mixed effects models will be used to analyze continuous variables with repeated measures (eg, scale scores at multiple time points). The models will include group, time, and their interaction as fixed effects; individual subject IDs and study centers will be incorporated as random effects.

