### Interim Analysis

One interim analysis is planned when approximately 50% of participants have completed the 3-month primary end point assessment. To control the overall one-sided type I error rate at 0.025, a group sequential approach based on the O’Brien-Fleming alpha-spending function will be applied, allocating one-sided nominal significance levels of 0.0026 and 0.0240 to the interim and final analyses, respectively.

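### One unrestricted one-sided P < .03 rule covers about ten secondary endpoints, while the only stated error control is across the interim and final looks

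*Protocol article*

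**What the plan says.** The Survival Outcomes subsection of Data Analysis describes Kaplan-Meier, log-rank and Cox analyses of 1-year OS and PFS. It ends with a general rule that a one-sided P "value of <.03 will be considered statistically significant". The Abstract (Methods) gives the same rule. Neither place restricts it to an endpoint.

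The secondary outcomes are PSQI, PHQ-9, GAD-7, the revised Piper scale, the EORTC core questionnaire, the TCM syndrome scale, actigraphy, the sleep diary, and 1-year OS and PFS. For repeated scores, the Secondary Outcome Analysis subsection specifies mixed models: "The models will include group, time, and their interaction as fixed effects".

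Elsewhere the protocol works at a different level. Sample Size has: "Assuming a one-sided significance level (α) of .025 and a statistical power (1-β) of .80". Interim Analysis controls the overall one-sided rate at 0.025 by "allocating one-sided nominal significance levels of 0.0026 and 0.0240 to the interim and final analyses, respectively".

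On the standing of the secondary outcomes, Objectives states: "The secondary objectives include assessing its impact on" quality of life and survival. The Abstract's conclusion expects the trial to "generate clinical evidence for a new therapeutic option that improves quality of life and alleviates the symptom burden". No passage says that secondary P values are descriptive or depend on the primary result.

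**The concern.** A rule that names no endpoint applies to all of them. Its position straight after the log-rank tests makes it hard to read as a rule for the primary endpoint only. The O'Brien-Fleming split protects against looking twice at the data. It does not protect against testing ten different outcomes.

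If the primary endpoint failed and, say, one symptom scale or PFS reached P < .03, the protocol's own text would allow that result to be reported as a statistically significant benefit. Quality of life and survival are stated objectives, so such a claim would carry weight. The protocol gives no error rate for it, and the threshold is looser than the one used to design the trial.

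**Working it through.** **Inputs from the protocol.** Threshold .03 (Survival Outcomes; Abstract). Design alpha one-sided 0.025, power 0.80, remission 10% against 40%, margin 15% (Sample Size). Nominal levels 0.0026 and 0.0240 at about 50% information (Interim Analysis). Ten secondary measures (Secondary Outcomes).

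**Assumption.** The protocol gives no correlations between endpoints. An equal correlation ρ is varied from 0 to 0.7.

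**Step 1: which level the design uses.** The unpooled superiority-by-margin formula at 0.025 gives n = (0.10×0.90 + 0.40×0.60) × (1.960 + 0.842)² / (0.40 − 0.10 − 0.15)² = 0.33 × 7.85 / 0.0225 ≈ 115.1, so 116 per group, and 116/0.80 = 145. Both match the protocol. At .03 the same formula gives 109. The trial was therefore sized at 0.025.

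**Step 2: what the group-sequential levels spend.** For two looks with correlation √0.5, the overall rate is 1 − P(Z₁ < c₁, Z₂ < c₂).
- Levels 0.0026 and 0.0240: 0.0250 overall, as the protocol intends.
- Levels 0.0026 and .03: 0.0309 overall.

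Using .03 at the final look would exceed the stated 0.025.

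**Step 3: family-wise rate across ten secondary tests, no true effect.** If independent, the rate is 1 − (1 − α)^10:
- α = .03: 1 − 0.97^10 = 26.3%
- α = 0.025: 1 − 0.975^10 = 22.4%

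If equally correlated, the rate is 1 − ∫ Φ((z₁₋α − √ρ·u)/√(1−ρ))^10 φ(u) du:

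| ρ | α = .03 | α = 0.025 |
|---|---|---|
| 0 | 26.3% | 22.4% |
| 0.3 | 20.7% | 17.8% |
| 0.5 | 16.6% | 14.4% |
| 0.7 | 12.4% | 10.7% |

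A separate simulation agreed to within 0.1 percentage point. Relative to 0.025, the extremes are 10.7/2.5 ≈ 4.3 and 26.3/2.5 ≈ 10.5.

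**Step 4: survival alone.** Two independent tests give 1 − 0.97² = 5.9% at .03, or 1 − 0.975² = 4.9% at 0.025.

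**The case against.** The strongest reply is that this is a condensed article and the SAP is not shown. A testing order for secondary endpoints, and the contrast that decides each mixed model, are commonly left to the SAP. That stands: their absence here is not an error, and it does not show that the trial lacks them. What remains is a rule the article does state. An SAP that follows it inherits the problem, and an SAP that adds a hierarchy contradicts it.

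A reader might also infer several stronger points that the document does not support.
- *A false benefit is likely.* With one test per endpoint the chance is at most about 26%.
- *Every scale at every visit is a separate test.* Counting the EORTC questionnaire as 15 scales gives 24 tests. Counting every scheduled visit gives 6×6 + 2×3 + 2 = 44. Under independence at .03 the rates would be 51.9% and 73.8%. But the description, "The items form 15 scales: 5 functional scales (physical, role, cognitive, emotional, and social), 3 symptom scales" and so on, explains how the instrument is scored and does not declare 15 endpoints. The mixed models do not plan visit-by-visit tests.
- *The survival conclusion carries many times the nominal error.* OS and PFS together give about 5% to 6%.
- *The secondary outcomes have no stated status.* There is one primary endpoint at one time point, and the rest are labelled secondary. That label does not, however, switch off an unrestricted significance rule.

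Finally, .03 may be a rounding of .025. That would explain the discrepancy, but the printed threshold is still the looser one.

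**Conclusion.** The point holds in a limited form. The protocol states one significance rule for every test, controls type I error only across the two looks, and does not make secondary claims depend on primary success. With ten secondary tests, one per endpoint, the chance of at least one false significant benefit is about 12% to 26% at .03, or 11% to 22% at 0.025, which is roughly 4 to 10 times 0.025. These figures rest on no true effect for any secondary endpoint and on assumed equal correlations from 0.7 to 0.

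Separately, .03 conflicts with the 0.025 in Sample Size and with the 0.0240 final level in Interim Analysis, so these passages must be reconciled. The primary test is not invalidated if it is judged at its group-sequential levels. What lacks protection is any claim of significance on a secondary endpoint.

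**What to change.** Replace the sentence in Survival Outcomes and in the Abstract with two statements.
1. The significance rule applies only to the primary endpoint, at its one-sided group-sequential levels of 0.0026 (interim) and 0.0240 (final).
2. All secondary outcomes, including quality of life, OS and PFS, are supportive. They are reported as estimates with 95% CIs and no claim of significance, unless the SAP prespecifies a multiplicity procedure that starts only if the primary endpoint succeeds.

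Which secondary endpoints to test, and in what order, can stay with the SAP. The change is a few sentences and needs no extra patients or data. It can be made before any results exist, since the article reports no recruitment as of April 2026. The downside is that fewer secondary results can be called significant.

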#### Formal Stopping Rules

The trial may be terminated early for overwhelming efficacy if the interim test statistic crosses the prespecified O’Brien-Fleming boundary (corresponding to a one-sided significance level of 0.0026), or for futility based on conditional power assessment, as determined by the Independent Data Monitoring Committee.

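### The stated significance threshold of one-sided P<.03 is incompatible with the overall one-sided error of 0.025 and the final nominal level of 0.0240

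*Protocol article*

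**What the plan says.** All places are in the protocol article.

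- **Survival Outcomes** (the last subsection before Interim Analysis) closes with a separate line declaring that a one-sided P "value of <.03 will be considered statistically significant". The **Abstract** (Methods) repeats the sentence after the outcomes, visits and software, and does not tie it to any end point.
- **Sample Size**: "Assuming a one-sided significance level (α) of .025 and a statistical power (1-β) of .80", which leads to 116 per group.
- **Interim Analysis**: "To control the overall one-sided type I error rate at 0.025", the plan uses one interim look at about half of the primary end point data, "allocating one-sided nominal significance levels of 0.0026 and 0.0240 to the interim and final analyses, respectively". The method named is "a group sequential approach based on the O’Brien-Fleming alpha-spending function will be applied".
- **Formal Stopping Rules** repeats the interim boundary, "corresponding to a one-sided significance level of 0.0026".
- **Primary Outcome Analysis** names the test and the confidence interval but gives no significance level of its own.

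**The concern.** The article contains two decision rules for the final primary test. Under the general sentence, success is one-sided P<.03. Under the group-sequential plan, it is P at or below 0.0240. Because Primary Outcome Analysis states no level, a reader who consults only that section and the general sentence would use .03.

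The rules disagree for any final P value between .0240 and .03. In that range, whether the trial met its primary end point would depend on which section was followed, and the choice would be made after the result was known. If the .03 rule won, the error rate promised in Interim Analysis would not be kept.

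**Working it through.** **Inputs.** Interim level 0.0026 and final level 0.0240, overall target 0.025, interim at about 50% of information (Interim Analysis). Competing level .03 (Abstract, Survival Outcomes). Remission rates 10% and 40%, margin 15%, one-sided .025, power .80, 116 per group (Sample Size).

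**Formula.** With no treatment effect, the interim and final statistics Z1 and Z2 are bivariate standard normal with correlation √t, where t is the information fraction at the interim. The overall one-sided error is 1 − P(Z1 < z1, Z2 < z2). At t = 0.5 the correlation is 0.707. The critical values are z(0.0026) = 2.794, z(0.0240) = 1.977, z(0.025) = 1.960 and z(0.03) = 1.881.

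**Step 1: reproduce the plan's own figure, then change only the final level.**

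| Interim level | Final level | Overall error, t = 0.50 | t = 0.45 | t = 0.55 |
|---|---|---|---|---|
| 0.0026 | 0.0240 | 0.0250 | 0.0252 | 0.0249 |
| 0.0026 | 0.025 | 0.0260 | 0.0261 | 0.0258 |
| 0.0026 | 0.03 | 0.0309 | 0.0310 | 0.0307 |

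The first row confirms that the Interim Analysis levels do what that section claims. In the last row the excess is 0.0309 − 0.025 = 0.0059, and 0.0059/0.025 is about 24%. Without any interim look, a single test at .03 has error 0.0300 by definition.

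**Step 2: which level was the trial sized at?** With unpooled variance, n per group = (z_α + z_β)² × [0.10×0.90 + 0.40×0.60] / (0.30 − 0.15)².

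- At α = .025: (1.960 + 0.842)² × 0.33 / 0.0225 = 115.1, so 116, as stated.
- At α = .03: (1.881 + 0.842)² × 0.33 / 0.0225 = 108.7, so 109.

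The stated sample size is reproduced at .025 and not at .03.

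**Step 3: the boundary label.** The classical two-look O'Brien-Fleming boundary at 50% information has final critical value 1.977 and interim value 1.977 × √2 = 2.797. The nominal levels are 0.00258 and 0.0240, which match the stated pair. The O'Brien-Fleming-type alpha-spending function spends 2 × [1 − Φ(z(0.0125)/√0.5)] = 2 × [1 − Φ(3.170)] = 0.0015 at t = 0.5 and leaves a final nominal level of 0.0245. Both pairs give 0.0250 overall at 50%. The label and the numbers therefore come from two different versions of the method, with no error cost at the planned look.

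**The case against.** The strongest reply is that .03 is an editorial slip. It equals .025 rounded to two decimals, every design figure uses .025, and the sample size reproduces only at .025. The group-sequential section sets a specific rule for the primary test, and a specific rule normally displaces a general sentence, here one placed under Survival Outcomes. On that reading the error is 0.0250.

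Much of this stands. A reader might infer that the trial's type I error is inflated. The article does not support that as a plain statement, because the inflation arises only if .03 governs the final primary test. A reader might also count three competing thresholds. That is one too many: .025 overall and 0.0240 at the final look are consistent parts of one design.

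The contradiction remains all the same. The article does not say that .03 is rounded, and rounding a significance threshold upwards loosens the rule. Reading it as .025 does not settle the final look either, since .025 after 0.0026 gives 0.0260. It cannot be confined to survival, because the Abstract states it without restriction. A separate statistical analysis plan could not agree with both statements.

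The boundary label might also be read as a breach of error control. It is not one at the planned look: with the stated levels, the error stays between 0.0249 and 0.0252 for a look at 55% to 45%. The separate question of changing the sample size according to the observed interim effect is not measured by this calculation, and no claim about it is made here.

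**Conclusion.** The point holds as a contradiction between decision rules. One-sided P<.03 cannot stand beside an overall one-sided error of 0.025 and a final level of 0.0240. The disputed range for the final primary P value is .0240 to .03. If .03 were applied after an interim look at 0.0026, the overall error would be 0.0309; under the Interim Analysis rule it is 0.0250. These figures assume two looks, the first at 50% of information, normally distributed test statistics and no change of sample size.

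Rounding is the likely origin of the .03, but that is an inference. The correction should be made before any data exist, because this threshold decides whether the primary end point is met. The article reports no recruitment as of April 2026. The mismatch between the boundary label and its numbers is a minor note.

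**What to change.** 1. Delete the .03 sentence in the Abstract and at the end of Survival Outcomes.
2. State once, in Primary Outcome Analysis or Interim Analysis, that the primary end point is tested at one-sided 0.0026 at the interim and 0.0240 at the final analysis, for an overall one-sided error of 0.025.
3. Give a separate one-sided level, such as 0.025, for the other tests.
4. Minor: either describe 0.0026/0.0240 as the classical two-look O'Brien-Fleming boundary at 50% information, or keep the alpha-spending function and compute the levels from it at the actual information fraction (about 0.0015/0.0245 at 50%).

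The cost is a text correction in two places and a few added sentences. Items 1 to 3 keep the levels already given in Interim Analysis, and nothing in the planned sample size or the conduct of the trial changes.

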### Interim Analysis

One interim analysis is planned when approximately 50% of participants have completed the 3-month primary end point assessment. To control the overall one-sided type I error rate at 0.025, a group sequential approach based on the O’Brien-Fleming alpha-spending function will be applied, allocating one-sided nominal significance levels of 0.0026 and 0.0240 to the interim and final analyses, respectively.

#### Sample Size Reestimation

An internal pilot design will be used for sample size reestimation based on the observed effect size at the interim stage. If the observed effect is smaller than initially assumed but still clinically relevant, the sample size will be adjusted using the formula: $N_{R}={\left(E_{0}/E\right)}^{2}\times N_{0}$, where $N_{R}$ is the adjusted sample size (capped at $2N_{0}$). On the basis of interim results, the Independent Data Monitoring Committee will evaluate the conditional power of the trial. If the power is insufficient, the committee will discuss the necessity of sample size adjustment or early termination.

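### The re-estimation formula has no term for the 15-point margin, and resizing on the observed effect leaves one-sided 0.025 unsecured for the margin hypothesis

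*Protocol article*

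**What the plan says.** Four sections of the Protocol article bear on this.

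- **Sample Size:** for the control arm, "The remission rate for the control group at 3 months is estimated at 10" per cent. For the effect, "We posited an absolute increase of 30% in the intervention group, corresponding to an expected remission rate of 40" per cent. The margin enters the sizing as a value "of 15% is prespecified and incorporated into the sample size formula". The error settings are given as "Assuming a one-sided significance level (α) of .025 and a statistical power (1-β) of .80". With these inputs, the software run "yielded a required sample size of 116 participants per group". The section then allows 20% dropout and settles on 316 patients in total.
- **Interim Analysis:** one look at about half the primary end point data. The stated aim is "To control the overall one-sided type I error rate at 0.025", and the one-sided nominal levels are 0.0026 (interim) and 0.0240 (final).
- **Sample Size Reestimation:** the basis is stated as "An internal pilot design will be used for sample size reestimation based on the observed effect size at the interim stage". The trigger for an increase reads "If the observed effect is smaller than initially assumed but still clinically relevant, the sample size will be adjusted using the formula". In symbols the rule is N_R = (E0/E)² × N0, with a cap of 2N0. The committee also looks at conditional power and may discuss a change of size. The section gives no values for E0, E, N0 or the floor for clinical relevance.
- **Primary Outcome Analysis:** a chi-square test of the difference in remission rates, with no margin mentioned.

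**The concern.** Scaling by (E0/E)² is right when the test is against zero, because the required N then varies with 1/E². For a test against a margin M it varies with 1/(E − M)², so the same shortfall in the effect needs a much larger increase. A rule meant to restore power would then leave the trial well short of it.

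There is also an error-rate question. An internal pilot in the usual sense re-estimates nuisance parameters, such as the pooled remission rate. This rule uses the treatment effect itself, by arm. The levels 0.0026 and 0.0240 give 0.025 overall only if the second-stage size does not depend on the first-stage effect. The control stated under Interim Analysis is therefore at stake, as well as the final sample size.

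**Working it through.** **Inputs.** From Sample Size: control 10%, assumed difference 0.30, M = 0.15, one-sided α 0.025, power 0.80, 116 evaluable per group, 316 enrolled, 20% dropout. From Interim Analysis: look at half the information, levels 0.0026 and 0.0240. From Sample Size Reestimation: the formula and its cap. Assumptions: E is the raw risk difference, the observed and true differences are equal, and the floor is varied because none is stated.

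**1. The plan's own N.** With V = p1(1 − p1) + p2(1 − p2) = 0.40×0.60 + 0.10×0.90 = 0.33:

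n = (1.960 + 0.842)² × V / (0.30 − 0.15)² = 7.849 × 0.33 / 0.0225 = 115.1, so 116. With 20% dropout, 116/0.80 = 145. Both figures are reproduced, so the margin is in the original sizing. The planned 316 patients leave 316 × 0.80 / 2 = 126.4 evaluable per group.

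**2. What the formula gives, and what the margin test needs.** Required n = 7.849 × V / (E − 0.15)². Power = Φ((E − 0.15)/√(V/n) − 1.96).

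| E | (0.30/E)² | (0.15/(E − 0.15))² | n per group from formula, N0 = 116 | n for 80% power | Power at the formula's n |
|---|---|---|---|---|---|
| 0.28 | 1.15 | 1.33 | 134 | 152 | 75% |
| 0.25 | 1.44 | 2.25 | 168 | 250 | 63% |
| 0.23 | 1.70 | 3.52 | 198 | 382 | 52% |
| 0.20 | 2.25, capped at 2 | 9.00 | 232 | 942 | 28% |

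Example at 0.25: V = 0.35×0.65 + 0.09 = 0.3175; √(0.3175/168) = 0.0435; 0.10/0.0435 − 1.96 = 0.34; power 63%. Starting from 126.4 per group, the formula gives 182 and 67% power at 0.25, and 253 (capped) and 31% at 0.20.

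**3. Type I error.** Without re-estimation, the bivariate normal probability for levels 0.0026 and 0.0240 at half information is 0.0250, as stated. With the formula, the interim z was integrated out: N is raised only when floor ≤ E < 0.30, and the pooled final z is tested at 0.0240. Control rate 10%, 116 to 158 per group:

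| Floor for clinical relevance | Error at a true difference of 15 points |
|---|---|
| 0 to 10 points | 0.029–0.030 |
| 15 points | 0.027–0.028 |
| 18 points | 0.025–0.026 |
| 20 points | 0.024–0.025 |
| 25 points | 0.024 |

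Binomial simulation with a 15-point floor gives 0.0283 (116 per group) and 0.0271 (158 per group), against 0.0252 and 0.0248 without re-estimation. At control rates of 20 or 30%, the integrated values are 0.028–0.029 at a 15-point floor and 0.025–0.027 at 20 points. The maximum for any unblinded rule with this cap is 0.0309.

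The dependence on the floor has a simple cause. Doubling N raises the chance of a final rejection under the null when the interim z is below about 1.2, and lowers it above. A low floor lets in the first kind of case and a high floor leaves mainly the second.

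**4. Same rule, test against zero.** Applied mechanically, the error is 0.020–0.025 at every floor tried, so there is no inflation.

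**The case against.** The strongest reply has four parts.

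- **E is not defined.** If E0 and E mean the excess over the margin, the scaling is right apart from a small change in variance. A reader might infer that the formula is wrong whatever E means, and the article does not support that. But it nowhere says that E is net of the margin, and the only effect it assumes in advance is the 30-point difference. The net reading would also leave the error question open: with a 15-point floor on the raw difference, the error at the margin is 0.026–0.029.

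- **The named final test has no margin.** Against zero the error is not inflated, so it would be too strong to say that type I error is broken outright. A reader might also infer that, under a zero-difference test, the trial would be doubled for nothing. On these inputs it would mostly meet the efficacy boundary (z = 2.794) first. With 63 per group at the interim, the pooled z is 3.36 at 25 points and 2.81 at 20 points. With 58 per group it is 3.22 and 2.69, so only the last just misses. The under-powering and the inflation both belong to the margin hypothesis.

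- **The full protocol or SAP may hold a combination test.** That is possible, and its absence from an article is no fault. It would remove the error-rate part of this point. It would not remove the conflict between the printed formula and the printed margin.

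- **Back-calculating the interim effect.** A reader might infer that anyone told the new N can recover the effect. That works only between about 21 and 30 points, because the cap sends every triggering effect below 0.30/√2 = 21.2 points to 2N0.

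**Conclusion.** The point holds in limited form. On the natural reading of E, the re-estimation rule does not match the design it is meant to protect. At a 10% control rate it leaves 63–67% power at 25 points and 28–31% at 20 points for the margin test. These are fixed-sample powers at one-sided 0.025, with observed and true differences equal.

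The rule is driven by the observed effect, so internal pilot is a misnomer, and the 0.025 stated under Interim Analysis is not guaranteed for the margin hypothesis. With a 10% control rate the excess is small: about 0.027–0.028 at a 15-point floor, up to about 0.030 for lower floors, and none from about 20 points. The committee's freedom to discuss a change on conditional power leaves the 0.0309 maximum open. No inflation arises against zero under the mechanical formula. The error-rate conclusion assumes that the pooled final data are tested at 0.0240 without stage weights, which is all the article describes.

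**What to change.** 1. State E0, E, N0 and the numerical floor for clinical relevance.
2. Base any increase on the effect net of the margin: either conditional power for the margin test, or ((E0 − M)/(E − M))² with the cap. If the cap stays at 2N0 (232 to 253 evaluable per group), say plainly that it cannot restore 80% power below about 25 points, where 250 per group are needed.
3. Align the test under Primary Outcome Analysis with the margin used for sizing.
4. Protect the error rate in one of two ways. Either use a combination statistic with prefixed stage weights (Cui-Hung-Wang or inverse normal) at the planned boundary, or replace the rule with blinded re-estimation from the pooled remission rate. The second is a true internal pilot.

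The cost is protocol and SAP wording, a short simulation, and a small loss of efficiency from the weighted test when N is raised. The Results section reports no recruitment as of April 2026, so the change can be made before any outcome data exist.
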